### Trial design {8}

The trial is designed as a two-arm, parallel-group, superiority, randomized trial with a balanced randomization 1:1 to group-based psychoeducation versus a waiting list [38]. The control waiting list group will be offered participation in group-based psychoeducation (active intervention) during the following half year. The trial is planned and will be conducted in concordance with the CONSORT 2010 Explanation and Elaboration: updated guidelines for reporting parallel group randomized trials [39].

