### Intervention description {11a}

Group-based psychoeducation for relatives. Group size: 20–40 relatives. Duration of intervention: six sessions over 6–10 weeks, each session is 2 h long including a 15-min break. The sessions are held by experienced clinicians from the Copenhagen Affective Disorder Clinic, one chief physician, and one nurse. Each session focuses on a specific topic, which the clinicians present and discuss using a presentation viewer. The sessions are interactive, and the participants are encouraged to ask questions during the presentations. During each session, the participants will have some discussions in smaller groups to reflect on topics raised during the session.

The topics of the sessions are:Introduction (Information about the clinic, introduction of the clinicians and participants, expectations alignments)Bipolar disorder (the diagnosis and challenges in diagnosis)Medical treatment (which medication is used and why)Psychological treatment (psychoeducation for patients)Living with a bipolar disorder (a guest lecturer with lived experience with BD tells his own story of living with BD)Being a relative.

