### Sample size {14}

According to prior analyses [73] mood instability in patients with BD varies on a scale from close to 0 to 10 with an average of 4.1 (SD = 2.6). Our power calculation is based on the assumption that group-based psychoeducation will be associated with a minimum decrease of 0.2 in mood instability compared to the placebo arm; for a power of 80% and a type 1 error risk of 0.05, we need to randomize a total of 126 patients (www.sample-size.net). Also, we need to adjust for situations where one patient has two involved relatives, making them interdependent (estimated to be 30%), and consider expected dropout (estimated to be 10%, as in our prior study [68]) resulting in a total sample size of 180. We expect 200 relatives to agree in participating in the RCT.

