## Assignment of interventions: allocation

### Sequence generation {16a}

On the webpage www.randomization.com, we produced a randomization plan. The random numbers allocated the participants in either intervention (1) or control group (2).

We chose to have block randomization to achieve equal sizes of the groups during the ongoing recruitment process. If two participants were related to the same patient, they would be grouped together, as they would not be independent participants.

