## Statistical methods

### Statistical methods for primary and secondary outcomes {20a}

#### Statistical analyses

Analyses will be conducted for the total sample of 200 relatives and their corresponding patients with BD. Two-level linear mixed-effect models will be used including a fixed effect of group (active group versus control) and a person-specific random effect allowing for individual variation in mood instability or other outcome measures.

In relation to hypothesis 3, it will be investigated whether mood instability in patients and relatives covary more than mood instability in patients and healthy control individuals (controls collected as part of the ongoing Bipolar Illness Onset (BIO) study in the Copenhagen Affective Disorder Clinic [77].

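### The primary model has no patient level, although relatives of one patient are allocated together and the protocol itself calls them dependent

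*Protocol article*

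**What the plan says.** Three statements in the protocol article bear on this.

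- **Allocation** (Sequence generation {16a}): "If two participants were related to the same patient, they would be grouped together, as they would not be independent participants". In a section on allocation, this means that both go to the same arm. For such pairs the unit of allocation is the patient.
- **Sample size** ({14}): an allowance is made for situations where "one patient has two involved relatives, making them interdependent (estimated to be 30" per cent). Together with 10% dropout, this takes the total from 126 to 180.
- **Analysis** (Statistical analyses, under {20a}): "Two-level linear mixed-effect models will be used including a fixed effect of group (active group versus control) and a person-specific random effect". The same sentence says that this effect is there to capture variation between individuals.

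The sections on estimating mood instability, on additional analyses {20b} and on non-adherence and missing data {20c} add no patient or family effect, no clustered variance and no rule of one relative per patient. Data management {19} states that the logbook records which patient each participant belongs to.

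**The concern.** The first two statements treat relatives of one patient as dependent. The third specifies a model in which they are independent. A person-specific random effect accounts for repeated values from one relative, but it cannot link two different relatives.

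When pairs share an arm and their outcomes are positively correlated, the second relative brings less new information than the model assumes. The standard error of the group effect is then too small, the confidence interval too narrow, and the type I error above its nominal 5%. The stated model serves the primary outcome and the relatives' other outcomes, and the error favours a positive finding in an unblinded superiority trial.

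**Working it through.** **1. The plan's own figures.** Sample size {14} gives "for a power of 80% and a type 1 error risk of 0.05, we need to randomize a total of 126 patients", for "a minimum decrease of 0.2 in mood instability compared to the placebo arm", and an SD of 2.6. Trial design {8} gives 1:1 allocation. With a two-sided test (sidedness is not stated):

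n per arm = 2 × (1.960 + 0.842)² × (2.6 / 0.2)² ≈ 2,653, or 5,306 in total.

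So 126 does not follow from these inputs. It does match a standardised difference of 0.5: 2 × (1.960 + 0.842)² / 0.25 = 62.8, so 63 per arm. That is a separate matter, and nothing below depends on it.

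The step that matters here does reproduce: 126 × 1.3 × 1.1 = 180.2, the stated 180. The plan therefore carries a factor of 1.3 for dependence between relatives.

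**2. Levels in the model.** With repeated values per relative, the two levels are observation and relative. With one aggregated rMSSD value per relative, as the section on estimating mood instability describes, the person effect cannot be separated from the residual, and the model reduces to a comparison of independent values. In neither case is there a patient level.

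**3. Design effect for pairs in the same arm.** With m relatives per patient (1 or 2):

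DE = 1 + ICC × (Σm² / Σm − 1)

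The protocol does not say what the 30% is a percentage of, so both readings are shown.

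- Reading A, 30% of patients have two relatives. Per 100 patients, Σm = 70 + 60 = 130 and Σm² = 70 + 120 = 190. DE = 1 + 0.4615 × ICC.
- Reading B, 30% of relatives are in pairs. Per 100 relatives there are 70 singles and 15 pairs, so Σm = 100 and Σm² = 70 + 60 = 130. DE = 1 + 0.30 × ICC.

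**4. Consequence.** The correct standard error is √DE times the one the model reports. The actual type I error of a nominal 5% test is 2 × (1 − Φ(1.96 / √DE)). The ICC values are assumptions.

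| ICC | A: DE | A: √DE | A: type I error | B: DE | B: √DE | B: type I error |
|---|---|---|---|---|---|---|
| 0.1 | 1.05 | 1.02 | 5.53% | 1.03 | 1.01 | 5.35% |
| 0.3 | 1.14 | 1.07 | 6.62% | 1.09 | 1.04 | 6.05% |
| 0.5 | 1.23 | 1.11 | 7.73% | 1.15 | 1.07 | 6.76% |
| 1 (limit only) | 1.46 | 1.21 | 10.5% | 1.30 | 1.14 | 8.56% |

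**5. Check by simulation.** About 180 relatives were simulated, with pairs allocated together, one value per relative, an unclustered t-test and 20,000 runs per setting. At ICC 0.1, 0.3 and 0.5 the type I error was 5.4%, 6.6% and 7.7% under reading A, and 5.5%, 6.0% and 6.8% under reading B. This agrees with the formula.

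**The case against.** *The sample size already allows for it.* For power it does. The factor 1.3 equals the design effect under reading B at ICC 1, and under reading A it covers any ICC up to 0.30 / 0.4615 = 0.65. But if the extra relatives are then analysed as independent, the standard error is still computed as if no pairs existed. Only the analysis can correct that.

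*An article condenses, and the analysis plan may settle this.* That would answer silence. Here the text states the number of levels and names the random effect, and both conflict with the allocation rule.

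*The effect is small, and its size is assumed.* This stands. Most patients contribute one relative, no ICC is given for any outcome, and the standard error is too small only where the correlation within a patient is positive.

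*A reader might go further and infer clustering by course.* Only the active arm attends courses of 20 to 40 people, in which "the participants will have some discussions in smaller groups to reflect on topics raised during the session". With an assumed 20 trial participants per course and an assumed ICC of 0.02 to 0.05, the variance inflation averaged over the arms would be (1 + 19 × ICC + 1) / 2 = 1.19 to 1.48. The documents give neither a number of trial participants per course nor an ICC, and they never describe people on the same course as dependent. With few courses that variance would also be poorly estimated. Leaving it out is therefore not shown to be an error.

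**Conclusion.** The stated model contradicts the trial's own allocation rule and sample-size reasoning, and it should be corrected. The size is modest. For ICC 0.1 to 0.5, standard errors are too small by about 1 to 10%, and the actual type I error lies between about 5.35% and 7.7%, depending on the ICC and on the reading of 30%.

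This rests on positive correlation between relatives of the same patient. The protocol supports that expectation by calling them interdependent, but gives no value. Two stronger inferences are not supported. One is that the error rate is above 5% for every relatives' outcome, since the correlation on each scale is unknown. The other is that it reaches 8.6 to 10.5%, since ICC 1 would require two different people always to have the same value. The design itself is not invalidated.

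**What to change.** In the Statistical analyses section, replace the two-level model with one that has a random intercept for the index patient above the person effect. Where an outcome has one value per relative, use either a patient random intercept or standard errors clustered by patient. State this before the blinded analysis is opened.

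No new data are needed, because the logbook already holds the patient link. The cost is one line in the specification and confidence intervals wider by about 1 to 11% for ICC 0.1 to 0.5. It would also help to state whether the 30% counts patients or relatives. A course effect in the active arm can be added as an optional sensitivity analysis.

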### Eligibility criteria {10}

Inclusion criteria: relatives of patients with BD who are affiliated with the Copenhagen Affective Disorder Clinic. It is the patients who decide which relatives they would like to invite for psychoeducation.Exclusion criteria: Insufficient Danish language, or age under 18 years.

Data from *patients* with BD are collected from the A-bipolar trial, which is another RCT that is currently running in the Copenhagen Affective Disorder Clinic [42].

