**Fig. 1 Fig1:**
[figure not shown]
Spirit study schedule of enrolment, interventions, and assessments

*Primary outcome*: Daily self-reported mood instability collected via the Monsenso app^1^ [43] for relatives during the period in which the participants are part of the research project.*Secondary outcomes*: Other critically daily self-reported smartphone-based data including daily activity level, anxiety, irritability, stress, cognition, sleep, alcohol consumption, caregiver burden, and medicine as reported in [44].

Clinically rated observer-based scores on the following three scales: Hamilton Depression Scale-6 items (HAM-D6) [45] (being more sensitive in RCTs than the HAM-D17 [46]), the Young Mania Rating Scale (YMRS) [47] and the Functional Assessment Short Test (FAST) (a 24-item interviewer-administered interview concerning autonomy, occupational functioning, cognitive functioning, financial issues, interpersonal relationships and leisure time) [48].

Self-assessed scores on the following questionnaires: Burden Assessment Scale [49], Perceived Criticism Measure [22, 50], Carer Quality of Life [51, 52], Carer-Self-Efficacy [34, 53], Bipolar Knowledge Scale [54], Short Form-12 [55, 56], Brief Symptom Inventory [57], Perceived Stress Scale [58], Mood Disorder Questionnaire [59], Major Depression Inventory [60, 61], Childhood Trauma Questionnaire (CTQ) [62]. When the questionnaires are repeated after the intervention, the.

participants are asked to complete a satisfaction survey on the psychoeducation. The satisfaction survey was developed in close collaboration with the clinicians from the Copenhagen Affective Disorder Clinic.

*Tertiary outcomes*: Automatically smartphone-generated data on physical [63], and social activity [64].

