## Assignment of interventions: blinding

### Who will be blinded {17a}

The study participants are not blinded. JRS is not blinded, but JRS attempts to minimize the potential influence by (a) assigning participants at the end of the inclusion visit, so that questionnaires and ratings at T0 are before the allocation. (b) JRS did not routinely check the participants’ group during the intervention.

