### Plans to promote participant retention and complete follow-up {18b}

We check weekly to see if the participants remember to record in the Monsenso App. If there is a lack of adherence, we contact participants by phone call or text message, whichever is most suitable in the case. JRS sends emails with a reminder and a link to the questionnaire in Redcap 1 to 2 weeks prior to follow-up interviews, thus increasing adherence. If a participant wishes to leave the study, the date and reason are noted in the primary logbook.

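### For the scales scored at T0 and again after the course, the stated model names only a group main effect; the plan should state a baseline-adjusted follow-up contrast

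*Protocol article*

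**What the plan says.** The Protocol article gives the treatment comparison in one sentence under Statistical methods {20a}: "Two-level linear mixed-effect models will be used including a fixed effect of group (active group versus control) and a person-specific random effect". It covers every outcome, "allowing for individual variation in mood instability or other outcome measures". The section on additional analyses {20b} adds only interactions with type of relative and cohabitation. No time, group-by-time or baseline term is named anywhere in the article.

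On timing, the blinding section {17a} states that "questionnaires and ratings at T0 are before the allocation". The outcomes section {12} describes a second completion: "When the questionnaires are repeated after the intervention". The retention section {18b} mentions "a reminder and a link to the questionnaire in Redcap 1 to 2 weeks prior to follow-up interviews", which implies that the interview ratings (HAM-D6, YMRS, FAST) are repeated too. The number of follow-up occasions is not in the text; the schedule is in Fig. 1, which is not shown.

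Under {20c}, missing data are treated as missing at random, without imputation.

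**The concern.** The treatment term that the article names is the main effect of group. For a scale measured once before allocation and again after the course, the quantity of interest is the group difference after the course. A group main effect equals that difference only if all modelled rows are post-allocation.

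A person random effect needs at least two rows per person. For the interview and questionnaire scales, the T0 score is the obvious second row, because the text describes no other repeated measurement unless there is more than one follow-up visit. Fitted that way, the model mixes a T0 difference with an expected value of zero into the treatment estimate. A real benefit on burden, self-efficacy, knowledge or functioning could then be reported at about half its size, or missed.

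**Working it through.** **Inputs from the Protocol article**
- Allocation is 1:1 (Trial design {8}: "balanced randomization 1:1 to group-based psychoeducation versus a waiting list").
- Dropout so far is 25 of 185, or 13.5% (Trial status). I take dropouts as having a T0 score and no later one.
- The sample size is 126 before inflation, so 63 per arm, and 180 to 200 planned (Sample size {14}).

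**Assumptions not given in the documents**
- A true post-course effect of 0.5 SD on a secondary scale.
- A within-person correlation r of 0.3, 0.5 or 0.7.
- Two-sided alpha of 0.05, and relatives treated as independent.

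**The plan's own figure.** The article gives no power for the secondary scales. Its 126 is for the primary outcome, under a "minimum decrease of 0.2 in mood instability compared to the placebo arm" with SD 2.6. The formula n per arm = 2(1.960 + 0.842)² × 2.6²/0.2² gives 2,653 per arm, so 126 does not reproduce. It is what a standardised difference of 0.5 needs: 2(1.960 + 0.842)²/0.5² ≈ 63 per arm. That mismatch is a separate matter. I use 63 per arm only as a reference size.

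**Step 1: what the group coefficient estimates if T0 is an outcome row.** Take a random intercept, group as the sole fixed effect, and T rows per person of which one is T0. A person with T rows has weight w(T) = T/(1 + (T − 1)r) and contributes an expected group difference of (T − 1)/T times the effect. With a share m having T0 only:

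factor = (1 − m) w(T) (T − 1)/T ÷ [(1 − m) w(T) + m w(1)]

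- T = 2, m = 0: (0 + 1)/2 = 0.50 at any r.
- T = 2, m = 0.135, r = 0.5: w(2) = 1.333, so 0.865 × 1.333 × 0.5 ÷ (0.865 × 1.333 + 0.135) = 0.577/1.288 = 0.448. For r = 0.3 and 0.7 it is 0.454 and 0.441.
- T = 3, m = 0: 0.667.
- T = 3, m = 0.135: 0.615, 0.604 and 0.593 for r = 0.3, 0.5 and 0.7.

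With time and group-by-time, with or without equal T0 means, the factor is 1.00 in every case. A mixed-model fit to one simulated data set (2,000 people, true effect 1.0, r = 0.5) gave 0.56 for group only and 1.09 for the longitudinal model with equal T0 means.

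**Step 2: power for an assumed 0.5 SD effect, 63 per arm, one post-course score, complete data**
- Group only, T0 as a row: effect 0.25, SE = √(2 × ((1 + r)/2)/63). At r = 0.5, SE = 0.154 and z = 1.62.
- Follow-up score alone: effect 0.5, SE = √(2/63) = 0.178, z = 2.81.
- T0 as covariate: effect 0.5, SE = √(2(1 − r²)/63). At r = 0.5, SE = 0.154 and z = 3.24.

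| r | Group only, T0 as a row | Follow-up alone | T0 as covariate |
|---|---|---|---|
| 0.3 | 41% | 80% | 84% |
| 0.5 | 37% | 80% | 90% |
| 0.7 | 33% | 80% | 98% |

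At 100 per arm the figures are 59, 53 and 48% for group only, 94% for follow-up alone, and 96, 98 and over 99% with the T0 covariate.

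**Step 3: the other readings.** With one follow-up score per person and no T0 row, the person variance and the residual variance cannot be separated, so the described two-level model cannot be fitted as such. With T0 as covariate and one follow-up score, the person effect is not needed. With one follow-up score, then, the sentence as written does not describe a suitable analysis of these scales.

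**The case against.** The strongest reply is that the article is condensed and its sentence is not exclusive. It says that the models will be used *including* a group effect, which leaves room for time or baseline terms in a fuller document. No section says that T0 scores are outcome rows; with T0 as covariate or follow-up scores only, nothing is halved. The sentence is also generic, and for the daily smartphone measures a two-level model is natural because each person supplies many rows.

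Most of this stands. A reader might infer that group is the only fixed effect and that the trial will report half of every effect. The documents do not support that: group is the only *named* fixed effect, and the dilution depends on how T0 enters. The factor of one half also needs exactly one follow-up row, which the text does not settle. Nor would the dilution inflate the type I error, since under the null both differences are zero in expectation.

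A reader might also extend the point to the primary outcome. The documents describe no T0 value for rMSSD, so there is no such row to dilute it, and the same holds for the daily outcomes.

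Lastly, patient data come from A-bipolar, "which is another RCT that is currently running in the Copenhagen Affective Disorder Clinic", and its allocation is not in the named model. Nothing links that allocation to the one in this trial, so leaving it out costs precision at most. Adjusting rMSSD for other T0 scores is likewise optional.

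What the reply does not remove is that the article names a specific treatment contrast, the group main effect. For scales with a T0 value that is a poor choice under either reading: it dilutes the effect or leaves a collected baseline unused.

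**Conclusion.** The point holds for the secondary interview ratings and questionnaires that have a T0 value, and only for those. If T0 scores are outcome rows and no other term is fitted, the group coefficient recovers about 0.50 of the post-course effect, with a range of 0.44 to 0.67. In the one-follow-up case, power falls to 33 to 41% for an assumed 0.5 SD effect with 63 per arm. If only the follow-up score is used, the estimate is unbiased under randomisation, and the loss is smaller: 80% power against 84 to 98%.

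The factor of 0.50 for one follow-up row with complete data holds at any correlation. The power figures rest on the assumed effect size and correlations and ignore dropout and the clustering of relatives within patients; they show scale and are not forecasts.

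**What to change.** State in the analysis section that, for every secondary outcome with a T0 value, the treatment effect is the group difference at follow-up. Estimate it in one of two ways:
- a regression of the follow-up score on group and the T0 score of the same scale; or
- a longitudinal mixed model with time and group-by-time, T0 means constrained equal between arms, and the person random effect kept, reporting the follow-up contrast.

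Keep the generic two-level sentence only for outcomes with repeated post-allocation rows, such as the daily measures. Also state in the text how many follow-up occasions there are and which one carries the contrast.

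The cost is analysis wording; the T0 scores are already collected. Since {17b} has the analyses run blinded to allocation, the wording should be recorded before the arms are revealed.

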#### Mood instability—a sensitive primary outcome measure in randomized controlled trials

We have selected mood instability as the primary outcome measure in the RCT as this has several advantages: mood instability has internal validity as a real-life measure for patients and high external validity as it reflects patients’ illness severity and functioning. Extensive evidence shows that mood stability is of core pathogenetic significance in BD [67, 70–73]. Thus, a substantial proportion of patients with BD and relatives experience subsyndromal daily mood swings that are associated with increased perceived stress, decreased quality of life and functioning [67, 73], and increased risk of relapse and hospitalization for patients [70–72]. Increased mood instability behaves as a genetic vulnerability trait for BD as it is present in remitted patients [73] and their unaffected relatives [67]. Accordingly, during the last decade, there has been a gradual shift from a focus on affective episodes to inter-episodic mood instability [74, 75]. Mood instability is currently considered a new treatment target in BD as it appears to be a more sensitive measure of outcome in RCTs than more conventional outcomes focusing on relapse or recurrence of affective episodes [74–76].

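### The primary model as described names no pre-allocation covariate, although the protocol identifies correlates of mood instability and appears to collect them at T0; the likely cost is some efficiency, not bias

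*Protocol article*

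**What the plan says.** All places are in the protocol article.

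- **Statistical methods {20a}, Statistical analyses.** The primary and other outcomes are to be analysed with two-level linear mixed models "including a fixed effect of group (active group versus control) and a person-specific random effect". No covariate is named. The only other terms planned are the interaction analyses in section {20b}, by type of relative and cohabitation.
- **Mood instability as primary outcome (under Outcomes {12}).** A substantial proportion of patients and relatives are said to have "subsyndromal daily mood swings that are associated with increased perceived stress, decreased quality of life and functioning".
- **Outcomes {12}.** The secondary outcomes include the Perceived Stress Scale, Carer Quality of Life, Short Form-12 and the observer-rated FAST. The wording "When the questionnaires are repeated after the intervention" shows that the questionnaires are also given earlier.
- **Blinding {17a}.** Participants are assigned at the end of the inclusion visit, "so that questionnaires and ratings at T0 are before the allocation".
- **Informed consent {26a}.** Staff who may perform inclusions are trained in the Hamilton, YMRS and FAST ratings, which fits with FAST being rated at inclusion.
- **Sequence generation {16a}.** Randomisation is in blocks; no stratification factor is described.

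**The concern.** In a randomised trial with a continuous outcome, adjusting for baseline variables that predict the outcome narrows the confidence interval without recruiting anyone. Here the protocol itself names three correlates of its primary outcome in the population being randomised, and it seems to hold all three before allocation. The model it describes mentions none of them.

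The usual best covariate, a baseline value of the outcome, does not appear to be available: allocation falls at the end of the inclusion visit and no app period before it is described. The T0 scores are therefore the main prognostic information in hand. At stake is the width of the interval for the primary contrast, and hence power.

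**Working it through.** **1. The plan's own sample size.** Sample size {14} gives a difference of 0.2, SD 2.6, power 80% and type 1 error 0.05 (taken as two-sided), with a total of 126.

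- Per arm, n = 2·SD²·(1.960 + 0.842)² / difference². With 0.2 and 2.6 this is 2 × 6.76 × 7.849 / 0.04 ≈ 2653, or 5306 in total. The stated inputs do not give 126.
- With a difference of 0.5 SD, n = 2 × 7.849 / 0.25 = 62.8, so 63 per arm and 126 in total. The figure 126 therefore implies 0.5 SD, whereas 0.2 / 2.6 is about 0.08 SD.

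The power figures below use 0.5 SD because 126 implies it, not because the protocol states it.

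**2. Gain from covariates.** Let R be the multiple correlation of the T0 covariates with a relative's mood instability (rMSSD). The documents give no value, so R is assumed from 0.1 to 0.5. I treat each relative as contributing one independent rMSSD value.

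- Residual variance factor: 1 − R². Standard error factor: √(1 − R²).
- Power at 63 per arm: Φ(0.5 / √((4/126)(1 − R²)) − 1.960).

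| R | 1 − R² | Fall in SE | Power at 126, 0.5 SD |
|---|---|---|---|
| 0 | 1.00 | – | 80.1% |
| 0.1 | 0.99 | 0.5% | 80.5% |
| 0.2 | 0.96 | 2.0% | 81.7% |
| 0.3 | 0.91 | 4.6% | 83.7% |
| 0.5 | 0.75 | 13.4% | 90.0% |

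**3. Cost of the covariates.** With k covariates the variance is inflated by about 1 + k/(N − k − 3).

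- Two covariates: 1 + 2/121 = 1.017 at N = 126; 1 + 2/175 = 1.011 at N = 180.
- Three covariates: 1 + 3/120 = 1.025 at N = 126; 1 + 3/174 = 1.017 at N = 180.

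Net variance factors for two covariates at N = 126 are 0.99 × 1.0165 = 1.006 (R = 0.1), 0.96 × 1.0165 = 0.976 (0.2), 0.91 × 1.0165 = 0.925 (0.3) and 0.75 × 1.0165 = 0.762 (0.5). So there is no net gain at 0.1 and a gain at 0.2 and above. After this cost, power at 0.5 SD is about 80%, 81%, 83% and 90% respectively.

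**4. Chance imbalance.** At N = 126 a standardised covariate difference between arms has SD √(4/126) = 0.18, with a 95% range of ±0.35. A difference at the edge of that range moves the unadjusted estimate by R × 0.35 outcome SDs: 0.03 (R = 0.1), 0.10 (0.3) or 0.17 (0.5).

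**5. On the stated inputs.** With 0.2 and SD 2.6, power at 126 goes only from 6.3% to 7.2% even at R = 0.5. Adjustment does not rescue the sample size.

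**The case against.** **The text does not exclude covariates.** The model is introduced with the word including, which need not be exhaustive. This is a condensed article, and an analysis plan that is not shown may list covariates. A reader might infer that the trial has decided on an unadjusted analysis; the documents do not support that. They show only that the primary model's terms are stated and that none of the protocol's own named correlates is among them. This objection stands as to wording.

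**Nothing here is invalid.** A reader might infer that a chance imbalance in stress or functioning biases the result. It does not: randomisation makes the unadjusted comparison valid, and its standard error already allows for such imbalance. This stands in full and limits the point to efficiency.

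**The gain is assumed.** The protocol reports an association but no correlation, and does not say that one T0 score predicts rMSSD over the following months. A reader might infer that the precision is free; at R = 0.1 it is not. This stands too, and is why the range starts at 0.1.

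**Timing is partly inferred.** The schedule figure is not shown, so that each instrument is given at T0 is read from sections {12}, {17a} and {26a}.

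What remains is a better method than the one described, using data apparently already collected.

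**Conclusion.** The point holds as one of efficiency. The primary model as described omits pre-allocation variables that the protocol itself associates with the primary outcome. Across R of 0.1 to 0.5 the standard error falls by about 0.5% to 13% before the covariate cost, so the benefit runs from nil to worthwhile, with a net gain from about R = 0.2. This rests on the assumed R, on one independent value per relative, on the instruments being given at T0, and, for the power figures, on the 0.5 SD implied by 126. The mismatch between 126 and the stated 0.2 with SD 2.6 is a separate and larger problem that this change would not cure.

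**What to change.** Before unblinding, state in the primary analysis that T0 Perceived Stress Scale and T0 FAST scores enter as fixed-effect covariates beside group. Fix both now, with no optional additions; leaving quality of life out keeps the cost to two terms and avoids a choice between its two instruments. Fill a missing T0 score with the overall mean of that score, calculated regardless of arm. Report the group-only model as a sensitivity analysis.

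The cost is about one line of text and two degrees of freedom. No new data are needed if both instruments were given at T0, as appears. Section {17b} keeps the statistical analyses blinded to allocation, so the choice can still be made without knowledge of results. If an existing analysis plan already specifies such covariates, the sponsor need only say so.
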